#### Other data to be recorded

2.7.3.

**Preoperative:** Baseline data, including demographic characteristics, basic vital signs, complications, and information related to anaesthesia and operation.

**Intraoperative:** Record vital signs and respiratory parameters every 10 min during anaesthesia, the type and dose of intraoperative medicines, intraoperative adverse events, total fluid volumes, and the durations of anaesthesia, surgery, and the recovery period.

**Postoperative:** The PACU stay period, medicine administration, Ramsay Sedation score and Wong-Baker Faces Scale scores recorded when the patient leaves the PACU.

**Follow-up:** Will be conducted during postoperative hospitalization and on the 30th day after the operation.

### Sample size calculation

2.8.

This study is a multicentre, prospective, randomized controlled trial. According to the pretest, the mean ± standard deviation of the perioperative cumulative hypothermia effect value (*Σ Δ*T_i_ × *Δ*t_i_, i = 1…, *n*) under passive warming measures is 12.2 ± 4.31, and using perioperative active warming strategies, it can be decreased by 15%. Considering a dropout rate of 20%, 400 subjects will be required with 90% power and an *α* level of 0.05. The sample ratios of the four centres are *Q*_1 _= *Q*_2 _= *Q*_3_= *Q*_4 _= 1/4N = 100.

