### Randomization and blinding

2.5.

This study applies a randomized stratified block design. According to the number of research centres, it is divided into four strata. In each stratum, the number of blocks is 2, and the length of the blocks is 4. The eligible children will be randomly assigned to Group A and Group C at a ratio of 1:1. The randomization will be completed by SAS software (SAS Institute Inc., USA). The allocation information will be concealed in sealed, opaque envelopes and opened by the anaesthesiologists in charge before the children enter the preoperative waiting room. To ensure the participants' safety and to complete warming measures, the anaesthesiologists in charge will not be blinded, and they will not participate in follow-up or results analysis. In addition, the allocation information will be blinded for patients and the researchers in charge of follow-up. The interim analysis will be completed by researchers independent of the overall trial process.

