### Statistical analysis

2.11.

Statistical analysis will be performed by SPSS software, version 24. (International Business Machines Inc., USA). Continuous variables will be reported as the mean ± standard deviation ($\bar{x}\pm s$) or medians and interquartile ranges. Categorical variables will be presented as numbers (proportion, %). The Kolmogorov-Smirnov test will be performed to detect the normal distribution of continuous variables. Student's t test will be used for normally distributed continuous variables, and the Kruskal-Wallis H test will be used for abnormally distributed data. The grade variables will be analysed using the Mann-Whitney U test. The chi-square test and Fisher's exact test will be used to analyse categorical variables. Repeated measures analysis of variance will be applied for the analysis of repeated measures data. *p* < 0.003 is defined as statistically significant in interim analysis, and the statistical significance of the final analysis is set at *p* < 0.05.

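### The sample-size statement in section 2.8 is internally inconsistent: its printed inputs need about 295 randomised children, not 400, and the article does not show which figure is misreported

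*Protocol article*

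**What the plan says.** Section 2.8 (Sample size calculation) of the protocol article bases the sample size on a pretest. It states that the cumulative hypothermia value "under passive warming measures is 12.2 ± 4.31, and using perioperative active warming strategies, it can be decreased by 15" per cent. It then says: "Considering a dropout rate of 20%, 400 subjects will be required with 90% power", at an alpha level of 0.05, with 100 children at each of four centres. Section 2.5 (Randomization and blinding) has children "randomly assigned to Group A and Group C at a ratio of 1:1". Section 2.11 (Statistical analysis) plans a t test for normally distributed data and a rank test otherwise, and says that "the statistical significance of the final analysis is set at" p < 0.05. Section 2.9 adds one interim look at half the sample, with O'Brien-Fleming-type spending.

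Sidedness is not stated. Section 2.8 gives no SD for the active arm and mentions no allowance for the interim look, for a rank test, for centre or for the age strata.

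**The concern.** Section 2.8 prints everything a two-mean calculation needs except sidedness, so a reader can repeat it. Repeating it gives a total about 105 lower than the one printed. The text says that 400 are required at 90% power, not that 400 gives at least 90%, so a reader will take 400 as the output of the inputs beside it.

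Two things are at stake. If the printed inputs are right, about 105 more children are randomised than the stated justification supports. If 400 is right, at least one printed design assumption is wrong or missing, and anyone who later compares the observed SD or effect with the planning values will use the wrong benchmark.

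**Working it through.** **Inputs.** From section 2.8: control mean 12.2, SD 4.31, 15% reduction, 90% power, alpha 0.05, 20% dropout. From section 2.5: 1:1 allocation. Assumed: a two-sided test and a common SD in both arms.

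**Effect.** Difference = 0.15 × 12.2 = 1.83. Standardised effect d = 1.83 / 4.31 = 0.4246.

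**Attempt to reproduce 400.** Normal approximation: n per arm = 2 × (1.960 + 1.282)² / d² = 2 × 10.507 / 0.1803 = 116.6, so 117 per arm and 234 evaluable. The exact t-test calculation gives 117.5, so 118 per arm and 236 evaluable. Dividing by (1 − 0.20): 236 / 0.8 = 295, or 296 with equal arms (the normal approximation gives 294). The printed 400 is not reproduced: 400 / 295 = 1.36, or 36% more.

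**Variants tried** (total randomised):

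| Variant | Total |
|---|---|
| Two-sided, 90% power, n / 0.8 | 294 to 296 |
| Dropout added as n × 1.2 | 282 to 283 |
| One-sided alpha 0.05 | 240 |
| Difference rounded to 1.8 | 304 |
| Final alpha 0.047 to 0.049 (interim look) | 296 to 300 |
| Active-arm SD scaled by 0.85 | 254 |
| Rank test, relative efficiency 0.955 | 310 |
| Rank test, worst-case efficiency 0.864 or a 15% uplift | 340 to 344 |
| 95% power instead of 90% | 364 to 366 |

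None comes within 3% of 400 (388 to 412). Some combinations that the article does not state do land there: for example, two-sided alpha 0.01 at 90% power with n × 1.2 gives exactly 400. Nothing in the article points to them as the source.

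**Power of 400 on the printed inputs.** After 20% dropout, 400 × 0.8 = 320, or 160 per arm. Normal approximation: √(160 / 2) × 0.4246 − 1.960 = 3.798 − 1.960 = 1.838, and Φ(1.838) = 96.7%. The t-based figure is 96.6%. If all 400 are analysed (200 per arm), power is 98.9%.

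**What would make 400 correct at 90% power.** With 160 per arm, the detectable standardised effect is 0.3635.
- Keeping SD 4.31: difference = 0.3635 × 4.31 = 1.567, and 1.567 / 12.2 = 12.8% reduction.
- Keeping the 15% reduction: SD = 1.83 / 0.3635 = 5.03.

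**The case against.** Four points can be made for the plan.

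First, the discrepancy is on the safe side. On the printed inputs 400 exceeds 90% power. If the primary outcome is analysed by a rank test at its worst-case efficiency, 160 per arm still gives about 94%. This stands, and it limits how serious the point is.

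Second, the article condenses a fuller protocol, which may contain a further allowance. That is possible, and it leaves the cause open. It does not remove the inconsistency, because the article prints a complete set of inputs and a result that does not follow from them.

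Third, the extra children receive measures that section 2.4 describes as routine and of little risk, and the interim rule in section 2.9 does not use the power figure. Both are fair. No decision rule in the article would change.

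Fourth, sidedness is unstated, so the two-sided assumption could be questioned. A one-sided test gives 240 and widens the gap.

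A reader might also infer that the stated 90% is the wrong figure and that 97% is the true design power. The article does not support that. It shows only that sample size, power, SD and effect cannot all hold together. If the design SD was really about 5.03, or the target reduction about 12.8%, then 90% is correct and one of the printed inputs is not. Nor can one say that the target effect is unknown: it is stated, as 15% of 12.2.

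**Conclusion.** The point holds as an arithmetic inconsistency in section 2.8. The printed inputs need 236 evaluable children, about 295 to 296 randomised, against a stated 400. Taken at face value, those inputs give 400 randomised children about 97% power rather than 90%. The result rests on a two-sided test, a common SD and dropout applied as n / (1 − 0.20); no alternative that was tried and is compatible with the stated alpha and power closes the gap.

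The error is conservative and leaves the primary comparison adequately powered if the inputs are right. Which item is misreported cannot be settled from the article. It should be fixed, because the sample-size justification cannot be reproduced as printed, but it does not compromise the trial's main test.

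**What to change.** Keep enrolment at 400. First go back to the source calculation and find the input or allowance that produced 400, such as an SD near 5.03, a reduction near 12.8%, or an inflation factor that was not printed. State it in section 2.8 in place of, or beside, the present figures, together with the sidedness of the test.

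Only if no such input exists, restate the section along these lines: 236 evaluable children (about 295 randomised) give 90% power for a 15% reduction with SD 4.31 at two-sided alpha 0.05; 400 are to be randomised, and with 20% dropout (320 evaluable) this gives about 97% power for the same reduction, or 90% if the SD is as large as 5.0.

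The order matters: printing 97% before checking the source could replace a genuine design basis with a back-calculated one. The cost is a check of the original calculation and a few sentences of text, with no change to enrolment or conduct.

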### Interim analysis

2.9.

This trial will conduct interim analysis when the sample size reaches 50% to compare the effect and safety between the two groups by preserving the sample size as much as possible. The interim analysis will be supervised by the independent data management committee (DMC). Except for the researchers directly involved in the interim analysis, other researchers in this trial will still be blinded to the allocation information. The trial will use the Lan-DeMets alpha spending function with an O'Brien-Fleming boundary to correct the test level of interim analysis, and the effective test level to terminate the trial is *p* < 0.003.

### Stratified analysis

2.10.

Owing to the significant differences in age and growth among the included children, we will conduct stratified analysis on toddlers aged 1–3, preschool children aged 3–6, and school-age children aged 7–12 to obtain the response of each age stratum to active warming strategies as much as possible.

### Statistical analysis

2.11.

Statistical analysis will be performed by SPSS software, version 24. (International Business Machines Inc., USA). Continuous variables will be reported as the mean ± standard deviation ($\bar{x}\pm s$) or medians and interquartile ranges. Categorical variables will be presented as numbers (proportion, %). The Kolmogorov-Smirnov test will be performed to detect the normal distribution of continuous variables. Student's t test will be used for normally distributed continuous variables, and the Kruskal-Wallis H test will be used for abnormally distributed data. The grade variables will be analysed using the Mann-Whitney U test. The chi-square test and Fisher's exact test will be used to analyse categorical variables. Repeated measures analysis of variance will be applied for the analysis of repeated measures data. *p* < 0.003 is defined as statistically significant in interim analysis, and the statistical significance of the final analysis is set at *p* < 0.05.

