#### Primary outcome

2.7.1.

Perioperative cumulative hypothermia effect value (*Σ Δ*T_i_ × *Δ*t_i_, i = 1…, *n*).

Note: When the body temperature at a certain time (i) is <36°C, hypothermia variation will be recorded as *Δ*T_i,_ (*Δ* T_i _= 36°C-T_i_), and the duration of this hypothermia variation will be recorded as *Δ*t_i_.

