## Discussion

3.

This trial aims to verify the feasibility and thermal insulation effect of perioperative active warming strategies by comparing them with traditional passive warming measures to further improve the prognosis of paediatric patients. The primary outcome is the perioperative cumulative hypothermia effect value (*Σ Δ*T_i_ × *Δ*t_i_, i = 1…, *n*), which is chosen because it can better quantify the level of IPH and can more effectively reflect the differences between the two groups. In addition, we combine multiple secondary outcomes to comprehensively analyse the prognosis, which will provide more clinical evidence about active warming strategies.

This study also has some limitations. First, we do not limit the surgery to a single category, which could be a confounding factor. However, considering the desire to validate the generalisability of the active warming strategy in this study, we wanted to cover a relatively wide range of types of paediatric procedures. Second, the population included in this study is children aged 1–12 years, who have a wide variation in age and growth. A stratified analysis will be conducted on children in different age levels. Third, this trial will perform perioperative real-time temperature monitoring with an axillary temperature sensor. Although the core body temperature is closer to the real temperature, awake children might not tolerate this method of temperature monitoring. Axillary temperature monitoring is relatively accurate and easy to tolerate, and we can additionally measure the nasopharyngeal core body temperature after anaesthesia induction for correction.

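### A normality pretest, not the plan, decides whether the primary comparison is of means or of ranks, and neither test uses the centre stratification

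*Protocol article*

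**What the plan says.** The Statistical analysis section (2.11) sets a two-step rule for continuous data. First, "The Kolmogorov-Smirnov test will be performed to detect the normal distribution of continuous variables". Then Student's "t test will be used for normally distributed continuous variables, and the Kruskal-Wallis H test will be used for abnormally distributed data". The rule does not name the primary outcome. That outcome is continuous, though, and the article gives no other method for it.

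The Primary outcome section (2.7.1) counts only time spent below 36°C: "When the body temperature at a certain time (i) is <36°C, hypothermia variation will be recorded as" the shortfall from 36°C, which is multiplied by its duration and summed. A child who stays at or above 36°C therefore scores zero.

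The Sample size calculation (2.8) uses a control mean of 12.2 (SD 4.31) and a 15% reduction, which is a difference in means.

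On the design, section 2.5 says: "This study applies a randomized stratified block design. According to the number of research centres, it is divided into four strata". Section 2.10 plans separate analyses in three age bands because of "significant differences in age and growth among the included children". The Discussion concedes of the case mix that "we do not limit the surgery to a single category, which could be a confounding factor". Section 2.11 contains no centre term, stratified test or covariate.

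Sections 2.9 and 2.11 set an interim look at half the sample with a threshold of 0.003 and a final threshold of 0.05. No separate test is named for either look.

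**The concern.** There are two separate problems.

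**The question is not fixed in advance.** A t test addresses the difference in mean cumulative hypothermia, which is what the trial was sized on. Kruskal-Wallis with two groups asks whether values in one arm tend to rank above those in the other. For a skewed outcome with a spike at zero these are different questions and can give different answers. Under the stated rule, the shape of the data decides which becomes the headline result. Because the rule is applied afresh at each look, the interim boundary and the final test could refer to different hypotheses. The section also does not say what happens if one arm passes the normality check and the other fails.

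**The analysis does not follow the randomisation.** Stratifying by centre balances the arms within centres, which removes centre differences from the true variability of the treatment contrast. An unstratified test leaves those differences in its standard error. If centres differ, that standard error is too large.

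**Working it through.** **Inputs from the article.** Control mean 12.2, SD 4.31 and a 15% reduction, so the difference is 0.15 × 12.2 = 1.83. N = 400, 1:1, 20% dropout, so 400 × 0.8 / 2 = 160 analysed per arm. Alpha is 0.05, taken as two-sided because the article does not say.

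**The plan's own figure.** n per arm = 2 × (1.960 + 1.282)² × 4.31² / 1.83² = 117 after rounding up. That gives 234 in total, and 234 / 0.8 = 293 with dropout. The stated 400 is not reproduced. That is a separate matter, and here it means only that power is ample: the standard error is 4.31 × √(2/160) = 0.482, and power is Φ(1.83/0.482 − 1.96) = 0.967.

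**Ignoring centre.** Let ρ be the share of outcome variance explained by centre. The article gives no value, so 10% and 20% are assumed, with 4.31 taken as the total SD.

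- Standard error too wide by the factor 1/√(1−ρ)
- True size = 2 × [1 − Φ(1.96/√(1−ρ))]
- True standard error = 0.482 × √(1−ρ)
- Power, unadjusted = Φ((1.83 − 1.96 × 0.482) / true standard error)
- Power, adjusted = Φ(1.83 / true standard error − 1.96)

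| ρ (assumed) | SE ratio | True size | True SE | Power unadjusted | Power adjusted |
|---|---|---|---|---|---|
| 0.10 | 1.054 | 0.039 | 0.457 | 0.974 | 0.979 |
| 0.20 | 1.118 | 0.028 | 0.431 | 0.980 | 0.989 |

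**How often the pretest changes the test.** This was simulated for one arm of 160, drawing from a normal distribution with mean 12.2 and SD 4.31, truncated at zero, with extra zeros added (400 runs). The shares of zeros are assumptions. The article does not say whether the Kolmogorov-Smirnov test is corrected for an estimated mean and SD (Lilliefors), so both versions are shown.

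| Added zeros | Normality rejected, uncorrected | Normality rejected, Lilliefors |
|---|---|---|
| 5% | about 1% | 29% |
| 10% | 12% | 82% |
| 15% | 69% | 98% |
| 20% | 97% | 100% |

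A modest change in the share of zeros, or in the version of the test, moves the trial from one analysis to the other.

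**Interim against final.** Comparing 80 with 160 per arm, the normality verdict differed in about 59% of simulated trials with 15% zeros (uncorrected), and in about 42% with 10% zeros (Lilliefors).

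**Do the two tests differ in practice?** With a gamma shape matched to the stated mean and SD, hardly: for a 15% reduction, power was 0.987 for the t test and 0.978 for Kruskal-Wallis. With an assumed 30% zeros and a more skewed positive part, the rule always chose Kruskal-Wallis, and power was 0.16 against 0.27 for the t test. These figures depend on the assumed shape. They show that the two tests are not interchangeable, but they do not predict this trial.

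**Type I error of the two-step rule.** Across the normal, gamma and zero-inflated shapes, with identical distributions in the two arms, it stayed between 0.050 and 0.055.

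**The case against.** The strongest reply is that section 2.11 is one generic paragraph in a condensed article. It does not mention the primary outcome or exclude an adjusted model, and covariates are commonly left to the statistical analysis plan. That stands for the choice of covariates: randomisation keeps the unadjusted comparison valid without age or surgery type, so including them is a recommendation. It does not dispose of the pretest, which is a stated rule. Nor does it dispose of centre, which follows from the stated design.

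It is also fair that a rank test is a legitimate primary test for a skewed outcome bounded at zero, and that naming Kruskal-Wallis for two groups is no error, since it equals the Mann-Whitney test without continuity correction. The defect is that the choice is left open. Age is not wholly neglected either, although separate analyses by age band do not adjust the overall comparison.

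A reader might infer more than the article supports:

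- **That false positives are inflated.** They are not. Ignoring centre is conservative, and the two-step rule held its level in simulation.
- **That the trial loses much power.** On the article's inputs power is already about 0.97 at 160 per arm.
- **That the mean difference will never be seen.** Section 2.11 allows reporting as mean and SD, or as median and interquartile range. What is not guaranteed is that the mean difference is the tested primary result.
- **That the plan names baseline temperature as a source of variation.** It does not. Section 2.7.3 lists only basic vital signs before surgery, without saying that a temperature is taken before warming starts.

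**Conclusion.** The point holds as a fault in how the primary analysis is fixed, and it should be corrected.

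The more important part is the pretest. The only method stated for the primary outcome lets the data choose between the comparison the trial was sized on and a different one, possibly choosing differently at the two looks. How likely this is depends on the share of children with a zero score, which the article does not give, and on which version of the normality test is run.

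The centre part is real but small. If centres explain 10–20% of the variance, the standard error is 5–12% too wide, true size is 3.9% to 2.8%, and adjustment adds about half to one percentage point of power. If centres do not differ, it has no effect. Neither part makes a positive result less trustworthy on type I error grounds.

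**What to change.** Remove the normality pretest for the primary outcome and state one primary analysis, used at both the interim and the final look:

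- a linear model of the cumulative hypothermia value on treatment, with centre as the stratification factor, plus age and surgery type, which the article itself raises as sources of variation or possible confounding;
- the adjusted mean difference with a robust or bootstrap 95% confidence interval, so that inference does not rely on normality;
- a centre-stratified rank test (van Elteren) as a sensitivity analysis.

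Add pre-intervention temperature as a covariate only if it is confirmed to be recorded before warming starts.

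The cost is a revised paragraph and a few lines of code. Centre, age and surgery type need no new data collection.

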#### Inclusion criteria

2.3.1.

(1)Paediatric patients ≥1 year old and ≤12 years old, no gender limitations;(2)Scheduled for elective non-cardiac and non-transplant surgery under general anaesthesia or general anaesthesia combined with other anaesthesia methods (The specific types of surgery include pediatric general surgery, pediatric neurosurgery, pediatric urological surgery, pediatric otorhinolaryngologic surgery surgery);(3)American Society of Anesthesiologists physical status of I–II;(4)Estimated operation time of >40 min; and(5)Growth according to the normal range of WHO Child Growth Standards.

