#### Secondary outcomes

2.7.2.

(1)Cumulative hypothermia effect value (*Σ Δ*T_i_ × *Δ*t_i_, i = 1…, *n*) in the preoperative waiting room, operating room, and PACU;(2)Difference value between intraoperative core temperature and axillary temperature;(3)Results of arterial blood gas analysis in the anaesthesia recovery period, including pH, lactic acid, and haemoglobin values;(4)Shivering score, Cornell Assessment of Pediatric Delirium score, and thermal comfort score in the anaesthesia recovery period;(5)Body temperature in the morning of the first day after surgery;(6)The incidence of incision infection during hospitalization;(7)The morbidity of major complications during postoperative hospitalization;(8)Length of stay and expenses;(9)All-cause mortality 30 days after the operation.

Note: a. Anaesthesia recovery period refers to the time from stopping anaesthetic infusion to the time when the children are completely conscious and fully awake. b. Major complications during postoperative hospitalization include postoperative pulmonary complications, arrhythmias requiring treatment, myocardial infarction, sepsis, renal failure, central nervous system events, anastomotic leakage, and accidental transfer to the intensive care unit.

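### Repeated measures ANOVA is fixed with no variables or time points named; applied to intraoperative series, it would drop children whose anaesthesia ends before the last time point

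*Protocol article*

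**What the plan says.** The Statistical analysis section (2.11) names one method for all serial data: "Repeated measures analysis of variance will be applied for the analysis of repeated measures data". It lists no variable and no time points for that method. The software is also named: "Statistical analysis will be performed by SPSS software, version 24".

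Four other places bear on what those data could be and how long each series would run:

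- **Other data to be recorded (2.7.3):** "Record vital signs and respiratory parameters every 10 min during anaesthesia". This is the only repeating schedule with a stated interval. It stands outside the outcome list. The same section also records "the durations of anaesthesia, surgery, and the recovery period".
- **Secondary outcomes (2.7.2), item 2:** "Difference value between intraoperative core temperature and axillary temperature", with no time points. Item 1 of that list is the cumulative value in each of three locations (waiting room, operating room, PACU).
- **Inclusion criteria (2.3.1):** "Estimated operation time of >40 min". This is a lower limit only, and four surgical specialties are admitted. The Discussion repeats that "we do not limit the surgery to a single category, which could be a confounding factor".
- **Primary outcome (2.7.1):** the "Perioperative cumulative hypothermia effect value", a single sum per child.

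**The concern.** Classical repeated measures ANOVA works on a rectangular table with one row per child and one column per time point. A row with an empty cell is deleted. With an open-ended range of operation lengths, a grid over the intraoperative period will have empty cells for children whose anaesthesia ended earlier, and any isolated missing reading has the same effect.

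The analyst then has two options if the method is kept on such a grid. One is to end the grid early, which discards the later temperature course. The other is to analyse only the children observed to the end of the grid. That subset is smaller, and it is selected on a quantity seen only after randomisation. The protocol's Introduction lists increased bleeding and delayed recovery among the consequences of hypothermia, so it cannot be taken for granted that observation length is unrelated to arm. Because no time points are stated, the choice could also be made once the durations are known.

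**Working it through.** **The plan's own figure.** There is none to reproduce: the document gives no sample size, power or precision for the repeated-measures analysis, and no distribution of durations. Everything numerical below is therefore an illustration under stated assumptions.

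**Step 1: which data could be meant.**

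| Candidate | Values per child | Loss from a short operation under ANOVA |
|---|---|---|
| Primary outcome | one | none; not a repeated measure |
| Secondary outcome 1, by location | three | none |
| Secondary outcome 2, at a few common events | a few | none |
| Secondary outcome 2, as an intraoperative series | varies with duration | depends on the grid |
| 10-minute vital signs and respiratory data | varies with duration of anaesthesia | depends on the grid |

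Only the last two rows are exposed.

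**Step 2: share of children with a complete series.** Assume that duration D is lognormal with median m and log-SD s, restricted to D > 40 min. The share reaching the end T of the grid is

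P(D ≥ T | D > 40) = [1 − Φ(ln(T/m)/s)] / [1 − Φ(ln(40/m)/s)].

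- Lower end (m = 60, s = 0.4, T = 120): 0.0416 / 0.8446 = 0.049, or 5%.
- Upper end (m = 180, s = 0.4, T = 120): 0.8446 / 0.9999 = 0.845, just under 84.5%, or 84%.

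Over m = 60, 90, 120 and 180 min with s = 0.4 and 0.6:

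| Grid ends at | Children with a complete series |
|---|---|
| 40 min | 100% |
| 60 min | 59% to nearly 100% |
| 90 min | 18% to 96% |
| 120 min | 5% to 84% |
| 180 min | under 1% to 50% |

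The 100% at 40 min follows from the assumption itself, because all durations are taken to exceed 40 min. The eligibility limit applies to the estimated operation time, so an actual operation can be shorter. On the other hand, the recordings run over anaesthesia, which lasts longer than the operation.

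**Step 3: what the loss costs in precision, in one example.** Simulation with 320 children (400 less 20% dropout), m = 90, s = 0.5, readings every 10 min from 0 to 120 min, assumed variances and 60 runs:

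| Analysis | Children used | Mean estimate (true 0.18) | SE of group difference |
|---|---|---|---|
| ANOVA on complete series | about 30% | 0.180 | 0.067 |
| Linear mixed model | all | 0.182 | 0.037 |

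The SE ratio is 0.067 / 0.037 ≈ 1.8, in line with 1/√0.30 = 1.83. Neither estimate is biased here, because duration was generated independently of temperature. The example therefore shows the loss of precision and says nothing about selection bias. Some mixed-model fits gave boundary warnings, so the SEs are approximate.

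**The case against.** The strongest reply is that the protocol never links ANOVA to the 10-minute recordings. It speaks only of repeated data in general. The 10-minute recordings are not an outcome, and secondary outcome 1, with three values per child whatever the operation length, is at least as natural a target. Secondary outcome 2 may be meant at two common events, since the Intervention section ties core temperature monitoring to the period after induction and before awakening. On either reading no child is lost for a short operation. Variables, time points and covariance structure are commonly left to an analysis plan, which is not shown here. A mixed model also has limits of its own: readings after anaesthesia ends do not exist, so it still needs a defined window and an assumption about duration.

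Most of this stands. A reader might infer that the plan commits ANOVA to the 10-minute series and so drops every child with a shorter operation. The document does not support that: the link is an inference, and the loss arises only when the grid runs past a given child's anaesthesia. Nor is the analyst forced to choose between truncation and deletion, because event-based points or a per-child summary avoid both. The missing time points alone would not be a finding.

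What remains is that the method itself has been fixed, for all repeated data. It fits one plausible use badly and offers no advantage that would justify fixing it: on balanced data a mixed model performs about as well, and on unbalanced data it keeps the children that ANOVA would delete.

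**Conclusion.** The point holds conditionally. If the stated method is used on intraoperative serial data, children whose anaesthesia ends before the last time point are lost, as are children with a single missing reading, unless the grid is shortened to a period that all reach. If it is used on location-based or event-based values, short operations cost nothing.

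The size depends on the grid and the durations, and the document fixes neither. The retained share of 5% to 84% at 120 min and the SE ratio of about 1.8 rest on assumed lognormal durations, assumed variances and a chosen grid. They show what could happen and are not properties of this plan.

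A reader might also infer that the trial's main result is at risk. It is not: the primary outcome is one sum per child and does not pass through this analysis. At most secondary outcome 2 and the descriptive series are exposed. The severity is minor, and the change is a cheap improvement.

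**What to change.** Replace the sentence in section 2.11 with wording such as:

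*Repeated measurements will be analysed with a linear mixed model (SPSS MIXED) with fixed effects for arm, time, arm by time and centre, and a within-child covariance structure. All available readings within a pre-stated common window, or at a pre-stated set of events (for example induction, end of surgery and PACU), will be used.*

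Name the variables it applies to, and say whether secondary outcome 2 is a series or a value at set events. Centre belongs in the model because randomisation is stratified by centre.

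The cost is one or two sentences, with the same data and software and no additional children. The downsides are slightly more model specification and an assumption that observation length is uninformative given the model. The mixed model does not remove that assumption. Using common events or a window that nearly all children reach reduces how much rests on it.
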